### Outcome Evaluation

#### Outcome Measures and Sources of Data

The evaluation of the iCanFit, physical activity-promotion program will be based on three datasets:

HBA surveys collected using the iPad at baseline and two follow-up surveys. As shown in Table 1, the survey includes demographic information, technology use and eHealth literacy [37], current level of physical activity [38], quality of life [39], patient-provider communication [40], perceived support from the health care team [41], and perceived social support for physical activity from the community [42]. All of these measures are based on validated scales with good validity and reliability. The first follow-up is a phone survey 3 months after baseline and the second follow-up is a clinic visit 6 months after baseline. This arrangement is based on the consideration that all overweight older adults are asked to visit their PCP at least every 6 months [27].Fitbit data. Two types of Fitbit data will be collected for evaluation: physical activity data recorded on Fitbit and patient interactions with the health coaches and peers in the iCanFit online community.Clinic data. We will collect patients’ weight and adverse events related to participating in the study from the EHRs at the clinic visits at baseline and at the 6-month follow-up.

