#### iCanFit 2.0 Intervention Protocol

As illustrated in Figure 3, the iCanFit 2.0 intervention protocol includes four steps. First, after the eligible participants complete the informed consent forms, they will complete an HBA on an iPad (see Multimedia Appendix 1 for sample screenshots), which takes about 15 minutes. Right after completion, patients will receive a printed copy of the HBA summary report with colorful charts of their current level of physical activity compared to the recommended physical activity levels (see sample summary reports in Multimedia Appendix 1). Meanwhile, the same report will be printed out in the office of the PCP with whom the patient has an appointment. Second, the patient brings the HBA report into his/her appointment with the PCP and the report serves as a natural conversation starter to facilitate patient-provider communication and joint goal setting. Third, right after the patient’s appointment with the PCP in the primary care clinic, a health coach will meet with the patient, further explain the HBA report, and ensure the patient has set a long-term physical activity goal, if the patient has not set one with the PCP. The health coach will give the patient a Fitbit Flex 2 (Fitbit Inc) (see Multimedia Appendix 2 and section below about the device) and demonstrate how to use the device. The health coach will also help the patient to create an account on the iCanFit online community. The health coach will advise on how to set short-term (eg, weekly) goals, track and sync data, share progress with family and friends via Facebook, and obtain personalized feedback on the iCanFit online community. The counseling session will last 30 minutes; a photo-illustrative brochure with instructions on how to use the Fitbit as well as account information and reminders will be given to the patient. Fourth, the health coach will constantly monitor patients’ use of the Fitbit and iCanFit online community. Patients will receive incentives (eg, online badges, virtual coins, and honor levels) for meeting physical activity goals and updating their progress. Any questions posted on the iCanFit online community will be answered by the health coach within 12 hours. If a patient is “idle” for 2 weeks, the health coach will call the patient to offer help and address the patient’s barriers. Patients will also receive a brochure of safety tips (see Multimedia Appendix 3), which details possible adverse events during exercise and how to take action depending on the situation. For adverse events that need immediate medical attention, patients are advised to go to the nearest emergency room. For nonurgent matters, they can contact the health coach, who can assist with scheduling a clinic appointment with the patient’s PCP.

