#### Comparator

The patients in the control group will receive usual care enhanced with a Fitbit Flex 2, as shown in Multimedia Appendix 2. The Fitbit Flex 2 was released in 2016, costs US $75, and weighs a quarter of an ounce. It is compatible with iPhones and Android phones, only needs to charge once a week, syncs automatically with mobile phones within 20 feet, and easily syncs to a computer with a USB port. It tracks steps taken, stairs climbed, calories burned, distance travelled, and sleep time. Figure 4 illustrates the process of the comparator protocol. After eligible patients provide informed consent, they will first complete an HBA on an iPad while waiting for their appointment. Unlike patients in the intervention group, patients in the control group will not receive any reports from their HBA; after their appointment with the PCP, they will receive a Fitbit Flex 2 and a brochure explaining how to use the Fitbit and the benefits of regular physical activity. Patients in the control group will not be given any information about the iCanFit online community; neither will they receive counseling or monitoring from health coaches. Similar to the intervention group, control group patients will receive the safety tips of exercise brochure.

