#### Patient Retention

To ensure we retain most of the patients during the intervention trial, the following measures were proposed. First, we will explain to the participants the longitudinal nature of the study during the informed consent and the fact that they will have a phone survey in 3 months and a follow-up clinic visit in 6 months. Second, 2 weeks prior to the follow-up survey or visit, we will remind the participants via SMS text message or phone call and help them schedule the appointment at their convenience. Third, for patients who do not comply with the intervention protocol, for example, do not wear the Fitbit constantly or do not sync the data in a timely fashion, we will send friendly reminders via SMS text message and motivate them with positive outcomes of physical activity and social support from the iCanFit community. Patients who continuously ignore our reminders and invitations—for 2 consecutive weeks—will be considered dropouts. We expect a 20% attrition rate at 6 months. Fourth, some participants might lose their Fitbit device during the trial. We will immediately replace a Fitbit if lost. Based on our prior experiences [35,36], less than 5% of participants may lose the mobile device during the trial. Finally, some overweight older adults may report discomfort in exercise. During the counseling by the health coach at baseline, we will advise participants to slowly increase their physical activity level and to monitor their heart rates. All participants will have a brochure of safety tips (see Multimedia Appendix 3) outlining typical adverse events and how to take appropriate actions in case of such an event. The patient is advised to go to the nearest emergency room for an event that needs immediate care. For nonurgent issues that require consultation with a PCP, the health coach will assist to schedule an appointment.

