## Results

The proposed protocol received a high score in a National Institutes of Health review, but was not funded due to limited funding sources. We are seeking other funding sources to conduct the project.

**Table 1 table1:** Data collected and instruments used in the survey.

Domain	Scale or indicators	Data collection mode	Number of items
Demographics	Age, gender, race/ethnicity, marital status, education, income, insurance, chronic conditions, and perceived health	Survey with patients at baseline	11
Technology use	eHealth literacy scale (E-HEALS), alpha=.78 [37]	Survey with patients at baseline	11
Physical activity	International Physical Activity Questionnaire, alpha=.76 [38]	Surveys with patients at baseline and follow-up	4
Quality of life (primary outcome)	12-Item Short Form Survey, alpha=.81 [39]	Surveys with patients at baseline and follow-up	12
Patient-physician communication	Provider Patient Communication Scale, alpha=.80 [40]	Surveys with patients at baseline and follow-up	4
Support from health care team	Patient Assessment of Chronic Illness Care (PACIC), alpha=.79 [41]	Surveys with patients at baseline and follow-up	11
Support from broader community	Perceived social support for diet and exercise, alpha=.78 [42]	Surveys with patients at baseline and follow-up	9
Total minutes of exercise per week	Total minutes of moderate-to-vigorous physical activity a week	Fitbit	Varies
Patient-provider communication	Number of questions sent by patient	iCanFit community	Varies
Patient engagement	Frequency of log-ins, syncs, and communication with iCanFit community and health coach	iCanFit community and follow-up survey	Varies
Moderate-to-vigorous physical activity (primary outcome)	Total minutes of moderate-to-vigorous physical activity a week	Fitbit	1
Overall experience with the iCanFit program	Experience of the intervention and follow-up, intention of continuing use of Fitbit and iCanFit community, and suggestions for improving the program	Follow-up survey	Varies
Secondary clinic outcomes	Weight, chronic condition, and number of sickness clinic visits and adverse events	Medical records	4

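### Adverse events come only from the health system's own records, a passive source likely to miss events and to capture them unequally by arm; the same few questions should be put to both arms

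*Protocol article*

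**What the plan says.** - **Source of adverse events.** Under Outcome Measures and Sources of Data, the Protocol article takes from clinic data "adverse events related to participating in the study from the EHRs at the clinic visits at baseline and at the 6-month follow-up". Table 1 (Results) has one row for these outcomes, "Weight, chronic condition, and number of sickness clinic visits and adverse events", with medical records as the collection mode.
- **Contacts shared by both arms.** "The first follow-up is a phone survey 3 months after baseline and the second follow-up is a clinic visit 6 months after baseline". The survey content is listed domain by domain in the same section and in Table 1, and adverse events are not among the domains. The nearest entry is an item on overall experience with the program.
- **Urgent events.** "For adverse events that need immediate medical attention, patients are advised to go to the nearest emergency room" (iCanFit 2.0 Intervention Protocol; Patient Retention says the same of all participants).
- **Non-urgent events, intervention arm.** "they can contact the health coach, who can assist with scheduling a clinic appointment". The coach also monitors use of the device and online community, and after 2 weeks of inactivity "the health coach will call the patient to offer help".
- **Control arm.** Controls get the device and the same safety brochure, but "neither will they receive counseling or monitoring from health coaches" (Comparator).
- **Non-urgent events, arm not named.** Patient Retention says: "For nonurgent issues that require consultation with a PCP, the health coach will assist to schedule an appointment". This follows a sentence about all participants.
- **Attrition.** Patient Retention expects 20% at 6 months. The limitations in the Discussion say that controls may drop out more often.

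**The concern.** The program encourages overweight people aged 60 or older to be more active, and the article itself foresees discomfort and adverse events during exercise. A reader of the trial will want to know whether the intervention arm had more of them. That comparison is sound only if an event has about the same chance of being recorded in either arm.

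The stated source does not secure this. It relies on an event producing an entry in one health system's records. Some events will not do so in either arm. The chance that a minor event does so plausibly depends on whether someone is in regular touch with the patient, and that is part of what the trial randomizes. A difference in recorded events could then reflect the coach's attention and not a difference in harm.

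**Working it through.** The article states no adverse event rate or capture rate, so there is no figure to reproduce. The check is mainly textual, followed by an illustration on assumed values.

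**Step 1: routes by which an event can enter the data.**

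| Type of event | Intervention | Control |
|---|---|---|
| Urgent | Nearest emergency room; recorded if the information reaches the system's record | Same |
| Non-urgent, patient seeks care | Clinic visit, with coach help in booking | Clinic visit; booking help unclear (Comparator against Patient Retention) |
| Non-urgent, patient does not seek care | A coach in contact may prompt a visit, for example on a call after 2 idle weeks | No coach monitoring or idle call |
| Asked about at 3 or 6 months | No adverse event item listed | No adverse event item listed |

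The first row loses events in both arms if the emergency room is outside the system; nothing stated brings outside records in. The third row differs by arm. The fourth row, the only one that could be the same by design, is empty.

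**Step 2: effect on the comparison.** Let p be the true 6-month risk in an arm and c the probability that an event is recorded. Expected recorded events = n × p × c.

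- With equal true risk, the apparent risk ratio = c(intervention) / c(control), whatever p is.
- With equal capture c in both arms, the risk ratio is unchanged, but the risk difference becomes c × (p1 − p0). Under-counting common to both arms shrinks the absolute excess without by itself creating a false one.

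**Step 3: illustration.** n = 311 per arm (622 / 2, from Power and Sample Size Calculations). Assumed, not from the document: p = 10% in both arms, so 311 × 0.10 = 31.1 true events per arm.

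| Capture, intervention / control | Recorded events | Apparent risk ratio |
|---|---|---|
| 80% / 80% | 24.9 / 24.9 | 1.00 |
| 80% / 65% | 24.9 / 20.2 | 0.80 / 0.65 = 1.23 |
| 80% / 60% | 24.9 / 18.7 | 0.80 / 0.60 = 1.33 |
| 80% / 50% | 24.9 / 15.6 | 0.80 / 0.50 = 1.60 |
| 60% / 40% | 18.7 / 12.4 | 0.60 / 0.40 = 1.50 |

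**Step 4: attrition.** If recording an event required attendance at the 6-month visit, the ratio from attrition alone would be (1 − dropout in intervention) / (1 − dropout in control). Two assumed splits that average the expected 20% (equal arms) give 0.85 / 0.75 = 1.13 for 15% against 25%, and 0.90 / 0.70 = 1.29 for 10% against 30%. This applies only if records are not reviewed for patients who miss that visit.

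**The case against.** Four objections have force.

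1. **Two visits need not mean two snapshots.** A reader might infer that events between baseline and 6 months are not looked at. The text does not support that. An electronic record runs continuously, and Table 1 counts sickness visits, which makes sense only over an interval. A 6-month extraction can cover all in-system care since baseline. This stands, so the weakness is the passive, in-system source and not the number of visits.
2. **Booking help may be open to controls.** Patient Retention names no arm, and Comparator excludes counseling and monitoring but does not mention booking. This stands as an ambiguity. It weakens one route to unequal capture but leaves monitoring and idle calls, which are confined to the intervention arm.
3. **The coach is not named as an adverse event source.** True. Unequal capture would arise indirectly, when coach contact turns a symptom into a clinic record.
4. **Survey answers have their own bias.** They are lost when a patient drops out, possibly more often in controls, and patients know what they received. This stands, and is why survey questions should not replace the records.

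It can also be said that harms are not a stated hypothesis and that the Data Analysis Plan makes physical activity the main goal. That lowers the weight of the point. It does not remove it, since Table 1 lists adverse events among the secondary clinic outcomes and fixes their source.

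**Conclusion.** The point holds as a design weakness in a stated method. Adverse events come from one health system's records and are limited to those related to participation. Under-counting is likely, and so is some inequality between arms, with more recorded events in the intervention arm as the likelier direction. This rests on two assumptions: that some events are treated outside the system or never lead to a visit, and that coach contact makes a clinic record more likely.

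Three stronger readings are tempting and not supported:

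- **A known size.** The ratios of 1.23 to 1.60 restate assumed capture rates. They show how the bias works, not how large it is here.
- **Relatedness judged with the arm known.** The article does not say who judges relation to the study, or with what masking.
- **Arm-unequal capture hiding harm of the intervention.** The coach mechanism points the other way. Missed outside emergency care could shrink an absolute excess, but nothing stated makes that loss differ by arm, and the article does not say whether outside records reach the system.

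**What to change.** - Add the same short set of adverse event questions to the 3-month phone survey and the 6-month visit in both arms: injury, fall, chest symptoms, and any emergency or urgent care anywhere since the last contact.
- Keep record review as a co-source. State that it covers the whole interval from baseline to 6 months for all enrolled patients, including dropouts where records allow.
- Report all events by arm regardless of judged relation to participation, with the source shown. List separately those known only through coach contact, since controls have no equivalent.
- Reconcile Patient Retention with Comparator on whether coach booking help is available to controls.

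The cost is a few more items in contacts that both arms already have. The downsides are a slightly longer survey, recall error, and missing answers for dropouts, possibly more of them in controls; the record review is kept to offset that last loss.

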#### Power and Sample Size Calculations

The primary outcome of the study is the total minutes of MVPA per week. MVPA is measured as “very active” and “fairly active” on Fitbit. The secondary outcome of the study is the patient’s self-report quality of life, measured by the 12-Item Short Form Survey [39]. We hypothesize the effect size of the iCanFit 2.0 to be 0.25, based on a prior Fitbit intervention trial [43]. Following the procedure developed by Cohen, the calculation of sample size is carried out in three steps by assuming a .05 significance level to achieve the power of 0.8 [44]. First, we assume that two independent samples can be obtained for the same size *n*_1_ each. Then the total sample size is *n*=2 x *n*_1_. In this ideal scenario, the total sample size *n*=398 is required to detect the effect size *d*=0.25 between the two population means. Second, because the randomization occurs at the clinic level, we need to consider the clustering effect. Previous similar research suggests a small clustering effect due to multiple patients per physician, but virtually no clustering effect between patients with different physicians in the same clinic [45]. We assume that if the intraclass correlation coefficient (ICC) per patient is equal to .05, and that ICC per physician is equal to 0, then equation 1 holds:

ICC=(1 + ICC_patient) x (1 + ICC_physican) – 1 = .05 (1)

Thus, the design effect is as follows in equation 2:

D=1 + (m - 1) x ICC (2)

where m is the average number of patients per physician in our effective sample. If we restrict m to be no more than 6, then D=1 + 5 x .05 = 1.25. We would need a sample size of 498 (ie, 398 x 1.25) after factoring in cluster effects. Third, based on our prior study of RCT primary care settings [36], we assume the attrition rate to be 0.2 after 12 months, thus the required sample size at baseline is 622 in total (ie, 498/[1-0.2]), or 52 patients per clinic on average. We will recruit no fewer than 30 and no more than 70 patients from each participating clinic.

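### The primary outcome is a weekly Fitbit total that falls with every unworn day, while support for using the device differs by arm, so a wear difference can appear as an MVPA effect

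*Protocol article*

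**What the plan says.** **Outcome.** Under Power and Sample Size Calculations: "The primary outcome of the study is the total minutes of MVPA per week". The next sentence gives the source: "MVPA is measured as “very active” and “fairly active” on Fitbit". Table 1, under Results, repeats the definition: "Total minutes of moderate-to-vigorous physical activity a week". Outcome Measures and Sources of Data, Table 1 and the Data Analysis Plan contain no minimum wear, no valid-day or valid-week rule, no scaling per worn day, and no way to tell zero activity from a device not worn.

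**Intervention arm.** Under iCanFit 2.0 Intervention Protocol, patients are shown how to use the Fitbit in a 30-minute session. After that, "the health coach will constantly monitor patients’ use of the Fitbit and iCanFit online community". There are rewards: "Patients will receive incentives (eg, online badges, virtual coins, and honor levels) for meeting physical activity goals and updating their progress". There is also follow-up of inactivity: "If a patient is “idle” for 2 weeks, the health coach will call the patient to offer help and address the patient’s barriers".

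**Control arm.** Under Comparator, controls receive the same device and a brochure, and "neither will they receive counseling or monitoring from health coaches".

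**Expected non-wear.** Patient Retention plans reminders for patients who "do not wear the Fitbit constantly or do not sync the data in a timely fashion". Those who ignore reminders for 2 consecutive weeks are classed as dropouts. The section does not name the arm that gets the reminders.

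**The concern.** A weekly sum of device minutes measures two things at once: how active the patient was, and how much of the week the device recorded. The second is supported by staff in one arm and left to a brochure in the other. If intervention patients wear the device more, their recorded totals are higher even when true activity is equal.

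The planned analysis does not remove this. A mixed model can accommodate missing observations under its assumptions, but a low total from a partly worn week is not missing. It enters as an observed value. The test is on the group-by-time term α3 in equation 3, so a wear gap that opens during follow-up goes straight into the tested parameter. No Fitbit week before the intervention is described that could absorb it: both arms receive the device after the recruitment appointment.

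At stake is the comparison that the Discussion lists as a strength, the program against the mobile device alone. The limitations do note that controls lack monitoring, but only as a cause of attrition and not as a problem in measuring the outcome.

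**Working it through.** **1. The plan's own figure.** Inputs from Power and Sample Size Calculations: d = 0.25, significance level .05 (sidedness not stated), power 0.8, equal arms, design effect 1.25, attrition 0.2.

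- A one-sided t-test needs 198.5, so 199 per arm and 398 in total, as stated. A two-sided test would need 506. Both versions are carried below because the text does not say which applies.
- 398 × 1.25 = 497.5, stated as 498.
- 498 / (1 − 0.2) = 622.5, stated as 622.

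The effective size after clustering and attrition is therefore 199 per arm.

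**2. Formula for the wear effect.** Assumptions, none taken from the article: no true difference between arms, unworn time contributes no minutes, unworn days are as active as worn days, and the SD is held fixed.

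Recorded mean = wear fraction × true mean, so

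spurious difference in SD units = (wear in intervention − wear in control) × mean / SD.

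**3. Example in days.** Assume a true mean of 60 min/week in both arms and an SD of 60.

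- Worn 6 v 5 of 7 days: 60 × 6/7 = 51.4 and 60 × 5/7 = 42.9. The difference is 60 × 1/7 = 8.6 min; 8.6/60 = 0.14 SD, or 57% of 0.25.
- Worn 6 v 4 of 7 days: 51.4 and 34.3. The difference is 60 × 2/7 = 17.1 min; 17.1/60 = 0.29 SD, more than the whole planned effect.

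**4. Range.** With SD equal to the mean (CV = 1), the standard error of the difference in SD units is √(2/199) = 0.100. For a spurious difference b, the one-sided false-positive rate is 1 − Φ(1.645 − b/0.100). The two-sided rate uses 1.960 and adds the small opposite tail.

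| Wear gap (percentage points) | Spurious difference (SD) | Share of d = 0.25 | False positives, one-sided .05 | False positives, two-sided .05 |
|---|---|---|---|---|
| 5 | 0.05 | 20% | 13% | 8% |
| 10 | 0.10 | 40% | 26% | 17% |
| 15 | 0.15 | 60% | 44% | 32% |
| 20 | 0.20 | 80% | 64% | 51% |
| 25 | 0.25 | 100% | 80% | 70% |

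For a 10-point gap, the spurious difference is 0.10/0.75 = 0.13 SD at CV 0.75 and 0.10/1.5 = 0.07 SD at CV 1.5.

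**5. What the table represents.** It treats the trial as a comparison of two means, as the plan's sample size does. Under equation 3, a gap that is constant from the first observation would fall in α1. The rates above apply to α3 only to the extent that the gap opens over time.

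**The case against.** The strongest reply is that the article names a construct and a source, not a processing algorithm. Minimum wear and the coding of empty days are often left to a full protocol or SAP, and a valid-week rule would be compatible with the stated outcome. This is fair as far as it goes. But the outcome is fixed twice as a weekly total, in a design that deliberately gives one arm staff support for generating the recorded data. Choosing the scale is then part of defining the outcome.

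Other parts of the reply stand and limit the point:

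- **Scoring.** A reader might infer that the plan scores non-wear as zero. It says no such thing; this follows only from summing minutes with no wear rule. Data never synced may be absent rather than zero.
- **Dropout.** A reader might infer that all non-wear stays in as low values. The 2-week rule in Patient Retention turns some prolonged non-wear into dropout.
- **Reminders.** A reader might infer that controls get no prompts at all. The reminder text speaks of the intervention protocol and the iCanFit community, which points to the intervention arm, but it names no arm. If controls also get reminders, the asymmetry shrinks; the difference in coaching and monitoring remains.
- **Target of the support.** The rewards are for goals and updates, and the call follows 2 idle weeks. Neither is aimed directly at one or two unworn days in a week.
- **Direction.** A reader might treat bias towards the intervention as certain. If low-wear controls are missing, those who remain may be the more motivated, which pulls the other way.

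**Conclusion.** The concern holds in a limited form. As stated, the primary outcome mixes activity with wear, and support for device use differs between arms by design. A wear difference can therefore be reported as an MVPA effect, and favouring the intervention is the more plausible direction.

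The article supports neither a specific size nor a claim that the result will be biased. On the assumptions of CV 1 and unworn days as active as worn ones, the rate of exchange is about 0.10 SD per 10 percentage points of wear gap, or 40% of the planned effect. It is 0.07 to 0.13 SD over CVs of 1.5 to 0.75. Gaps of that order are enough to matter, and the definition is easy to improve, so it should be changed before enrolment.

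**What to change.** 1. Define the primary outcome as mean MVPA minutes per valid wear day, multiplied by 7.
2. Prespecify one valid-day rule and one valid-week rule, derived from recorded device movement and applied identically in both arms. The Comparator section lists steps and distance among the tracked quantities but not wear time, so confirm that the rule can be computed. The article gives no thresholds; the team must choose and justify them.
3. Treat weeks below the minimum as missing, not zero, and state how unsynced periods are handled.
4. Report wear and the number of valid weeks by arm.
5. Add sensitivity analyses to the missing-data assumption, for example by varying the valid-day threshold and imputing under missing-not-at-random. Do not adjust for wear days: they arise after randomisation and may be affected by the intervention, so adjustment can itself bias the comparison.
6. Use the International Physical Activity Questionnaire, already collected at baseline and follow-up, as a supporting check. It does not depend on wear, but it is self-reported.
7. State in Patient Retention which arm or arms receive the wear and sync reminders.

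**Cost.** Mainly a data-processing rule and some extra analysis; the article says funding is still being sought, so the change is early. The downside is that some weeks become missing, possibly more in the control arm. Scaling by valid days also assumes that unworn days resemble worn ones, which is why item 5 is needed.

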where α_0_, α_1_, α_2_, and α_3_ are the fixed effects, ζ_ij_ is a random effect (ie, random intercept) for each PCP in each clinic, and ε_ijt_ is the residual error for repeated observations over time. The random effect is assumed to be normally distributed with mean zero. The residual error is assumed to be multivariate normally distributed across repeated observations, with mean zero and a covariance matrix that models the autocorrelation among repeated observations [46]. We will examine model fit statistics to choose an appropriate covariance structure. Hypothesis testing will be carried out to test for intervention effects on the outcome of interest over time. Referring to equation 3, this is equivalent to testing the hypothesis H_0_: α_3_ = 0. If higher outcome values are desirable, then a positive significant α_3_ parameter indicates a positive intervention effect (ie, we reject H_0_: α_3_ = 0). We will use the SAS version 9.0 (SAS Institute Inc) PROC MIXED procedure and PROC GLIMMIX procedure to fit multi-level models to continuous and binary data, respectively.

We will also apply structural equation modeling (SEM) to examine the extent to which the intervention takes effect at individual, interpersonal, health care, and community levels as shown in Figure 1. Models will be constructed to measure direct and indirect effects. We will also analyze whether increased MVPA is a mediator for improved clinical outcomes. Latent variables are similar to random effects, accounting for nested observations. We will use Mplus version 3.1 (Muthén & Muthén) to fit SEM for continuous and binary data [47,48].

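### The base sample size of 398 is the one-sided figure; with a two-sided .05 test the stated 80% power is about 70%

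*Protocol article*

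**What the plan says.** Under Power and Sample Size Calculations, the protocol article takes a standardised effect of 0.25 and two independent groups of equal size, and proceeds "by assuming a .05 significance level to achieve the power of 0.8". It then says that "the total sample size *n*=398 is required to detect the effect size *d*=0.25 between the two population means". This base figure is multiplied by a design effect of 1.25 to give 498, and divided by 0.8 for attrition to give 622 at baseline, or 52 per clinic. Nothing in the section says whether the .05 is one- or two-sided.

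Under Data Analysis Plan, the study hypothesis is worded directionally: more weekly moderate-to-vigorous activity with the intervention. The test itself is set on the group-by-time coefficient of the multi-level model: "this is equivalent to testing the hypothesis H_0_: α_3_ = 0". A significant coefficient with a positive sign is then read as benefit. No one-sided alternative or one-sided rejection rule is given.

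On attrition, the power section says "we assume the attrition rate to be 0.2 after 12 months", whereas Patient Retention says "We expect a 20% attrition rate at 6 months". The last planned follow-up is at 6 months.

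**The concern.** An unqualified .05 level paired with a point null is conventionally read as a two-sided test. A standardised difference of 0.25 with 80% power then needs roughly 250 per arm, not 199. If the sample size was solved for one test and the analysis will run another, the trial does not have the power printed for its primary outcome. A null result would be weighed against a 20% false-negative risk when the actual risk on this calculation is 30%. The Results section says that funding is still being sought, so funders may rely on the figure, and it can still be corrected.

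**Working it through.** **Inputs**, all from Power and Sample Size Calculations: d = 0.25 (SD = 1), alpha = .05, power = 0.8, allocation 1:1, stated base total 398 (199 per arm), design effect D = 1.25, attrition 0.2, 12 clinics.

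**Formula (normal approximation).** n per arm = 2(z_alpha + z_0.8)²/d², with z_0.8 = 0.8416 and 2/d² = 2/0.0625 = 32. The exact version solves the noncentral-t power of the two-sample t test with noncentrality d√(n/2).

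**1. Reproducing 398.** One-sided .05, z_alpha = 1.6449:
- Normal: 32 × (1.6449 + 0.8416)² = 197.8, so 198 per arm, 396 in total.
- t test: 198.52, so 199 per arm, **398 in total**. This is the plan's figure exactly.

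**2. The same inputs, two-sided.** z_alpha/2 = 1.9600:
- Normal: 32 × (1.9600 + 0.8416)² = 251.2, so 252 per arm, 504 in total.
- t test: 252.13, so 253 per arm, **506 in total**.

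The gap is 506 − 398 = 108 patients, or 108/506 = 21% of the two-sided requirement. That is too large for rounding or the choice of approximation to explain.

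**3. Power at 199 per arm.** The noncentrality is 0.25 × √(199/2) = 2.494.

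| Test at .05 | Normal | t test |
|---|---|---|
| One-sided | 0.802 | 0.801 |
| Two-sided | 0.703 | 0.701 |

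**4. Effect detectable with 80% two-sided power at 199 per arm.** Normal: (1.9600 + 0.8416) × √(2/199) = 0.281. t test: 0.2815.

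**5. Carry-through to enrolment.**
- The plan's chain: 398 × 1.25 = 497.5, so 498; 498/0.8 = 622.5, printed as 622; 622/12 = 51.8, so 52 per clinic.
- Backwards: 622 × 0.8/1.25 = 398 effective patients. Two-sided power at full enrolment, on the plan's own D and attrition, is therefore also about 0.70.
- Two-sided chain from 506: 506 × 1.25 = 632.5, so 633; 633/0.8 = 791.25, so 792; 792/12 = 66 per clinic. The stated maximum of 70 per clinic allows 12 × 70 = 840.

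**6. Attrition horizon.** The rate is 20% in both places, so replacing 12 months with 6 months leaves 622 unchanged.

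**The case against.** The strongest reply is that nothing was miscalculated. The power section never says two-sided, and under a one-sided .05 test 398 is exactly right and everything after it follows. The hypothesis is directional, a positive significant coefficient is what counts as success, and a null of zero can be paired with either kind of alternative. That PROC MIXED reports two-sided tests for fixed effects by default is a software convention and not a statement in the plan. The article is also a condensed account, so a fuller document might declare the sidedness.

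Part of this stands. The fault is best described as an undeclared one-sided calculation, not a two-sided one solved wrongly, and the 70% figure depends on the test being two-sided. But a directional hypothesis is not a one-sided rejection rule. The section that defines the test gives only a point null and looks at the sign once significance has been reached, which is how a two-sided test is read. Nor does the point rest on missing text: the article prints a specific number with its inputs, and that number does not match the usual reading of the test specified in the same article.

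A second objection is also fair. The 70% belongs to the simplified two-sample formula with D = 1.25. The randomised unit is the clinic, with about 52 patients, whereas D is built on 6 patients per physician, and the planned test is a group-by-time term in a repeated-measures model. The 70% is therefore a like-for-like correction of the printed 80%, not a forecast of the power of the final analysis.

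**Conclusion.** The concern holds. With d = 0.25, alpha .05, 80% power and equal arms, 398 is the one-sided t-test figure; the two-sided figure is 506. No one-sided test is declared, so on the conventional reading the stated power of 80% is really about 70%, the false-negative risk is 30% rather than 20%, and the effect detectable with 80% power is d = 0.28 rather than 0.25. The shortfall passes unchanged to the 622 enrolled.

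This assumes a two-sided .05 test and takes the plan's design effect of 1.25 and 20% attrition as given, without endorsing either. If a one-sided .05 test is intended and declared, 398 is correct. The mismatch between 12-month and 6-month attrition is a real inconsistency, but it changes no number and the conclusion does not depend on it.

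**What to change.** State the sidedness of the .05 test in both Power and Sample Size Calculations and Data Analysis Plan.

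- **If two-sided:** keep 622 and restate what it provides, namely about 70% power for d = 0.25, or 80% power for d = 0.28, under the plan's own D = 1.25 and 20% attrition.
- **If one-sided .05 is really intended:** say so in both sections; 398 and 622 then stand.
- **If 80% two-sided power for d = 0.25 is to be kept:** on the same inflation factors the chain is 506, 633 and 792 at baseline, about 66 per clinic, which the existing cap of 70 permits.

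In the same edit, change the attrition horizon in the power section to 6 months so that it agrees with Patient Retention and the follow-up schedule.

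The minimum correction is a restated figure and a few words. It needs no additional patients; the cost is that the published power becomes less favourable. Only the third option raises recruitment, by 792 − 622 = 170 patients.
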